## Abstract

**Background:**

Management of Type 1 diabetes comes with substantial personal and psychological demands particularly during adolescence, placing young people at significant risk for mental health problems. Supportive parenting can mitigate these risks, however the challenges associated with parenting a child with a chronic illness can interfere with a parent’s capacity to parent effectively. Interventions that provide support for *both* the adolescent and their parents are needed to prevent mental health problems in adolescents; to support positive parent-adolescent relationships; and to empower young people to better self-manage their illness. This paper presents the research protocol for a study evaluating the efficacy of the *Nothing Ventured Nothing Gained* online adolescent and parenting intervention which aims to improve the mental health outcomes of adolescents with Type 1 diabetes.

**Method/Design:**

A randomized controlled trial using repeated measures with two arms (intervention and wait-list control) will be used to evaluate the efficacy and acceptability of the online intervention. Approximately 120 adolescents with Type 1 diabetes, aged 13–18 years and one of their parents/guardians will be recruited from pediatric diabetes clinics across Victoria, Australia. Participants will be randomized to receive the intervention immediately or to wait 6 months before accessing the intervention. Adolescent, parent and family outcomes will be assessed via self-report questionnaires at three time points (baseline, 6 weeks and 6 months). The primary outcome is improved adolescent mental health (depression and anxiety). Secondary outcomes include adolescent behavioral (diabetes self-management and risk taking behavior), psychosocial (diabetes relevant quality of life, parent reported child well-being, self-efficacy, resilience, and perceived illness benefits and burdens); metabolic (HbA1c) outcomes; parent psychosocial outcomes (negative affect and fatigue, self-efficacy, and parent experience of child illness); and family outcomes (parent and adolescent reported parent-adolescent communication, responsibility for diabetes care, diabetes related conflict). Process variables including recruitment, retention, intervention completion and intervention satisfaction will also be assessed.

**Discussion:**

The results of this study will provide valuable information about the efficacy, acceptability and therefore the viability of delivering online interventions to families affected by chronic illnesses such as Type 1 diabetes.

**Trial registration:**

Australian New Zealand clinical trials registry (ANZCTR); ACTRN12610000170022

## Background

Type 1 diabetes (T1D) is a serious, life-long chronic illness most often emerging before or during adolescence. With a population prevalence between 136 (USA) and 428 (Finland) of 100,000 children and increasing global incidence, T1D is one of the most significant chronic illnesses emerging in childhood [1]. Treatment of T1D is intensive and ongoing, requiring a strict daily regimen of insulin injections and monitoring of blood glucose levels and dietary intake to avoid episodes of extremely high or extremely low blood glucose, both of which can be life threatening [1]. T1D is associated with serious long-term health complications such as kidney and heart disease, circulatory problems, retinopathy, and neuropathy [2] and a range of co-morbid mental health disorders including depression, anxiety, conduct and eating disorders [3-6]. A number of large scale trials have shown that optimal metabolic control, achieved through intensive disease management, reduces the risk of long term health complications (e.g., the Diabetes Control and Complications Trial [7]). However, intensive diabetes self-management imposes significant personal and psychological demands and is difficult to sustain.

Diabetes self-management has been shown to be particularly poor during adolescence [4], a time when young people undergo significant social, emotional and physical changes. These changes can sometimes result in the development of mental health difficulties or the commencement of dangerous risk taking behaviors (e.g., alcohol and other drug use) [4-6,8].

### Mental health outcomes for adolescents with T1D

The inter-relationship between mental health and physical health outcomes in adolescents with T1D is complex. Co-morbid depression and anxiety in adolescents with T1D has been associated with poorer disease adjustment and metabolic control [9], and more frequent hospitalization [10]. Conversely better metabolic control has been found to be associated with higher levels of internalizing symptoms [11] and meticulous adherence to diabetes self-care has been linked to higher anxiety [12], suggesting there is a psychological burden in maintaining the strict treatment regimen required to achieve optimum control. Indeed, evidence emerging from a number of longitudinal studies suggests that adolescents with T1D are more than twice as likely to develop serious mental health outcomes (e.g., mood, anxiety, eating or behavior disorders) than their non-diabetic peers [5]. The health of adolescents with T1D can also be compromised by risk taking and other health compromising behaviors often apparent in adolescence (e.g., alcohol consumption, poor eating and sleep practices). It is therefore critical to better understand how to support young people with T1D to manage those risks and to engage in health promoting behaviors.

### Family interventions to support adolescents with T1D

Parents are one of the primary influences on their children and play a critical protective role in mediating the health and well-being of their adolescent children [13,14]. For example, parent-adolescent relationships that are warm, loving, and involve clear boundaries and effective monitoring are associated with the development of resilience and effective coping resources in the adolescent [15,16]. Among adolescents with T1D, supportive parenting is associated with improved diabetes management and quality of life [17-20]. In addition, examination of parent-adolescent transactional processes has revealed that increased parent distress is associated with poorer adjustment in adolescents with T1D (e.g., [21,22]).

Parenting an adolescent with T1D can be challenging in that parents must adapt their parenting to include attention to their child’s medical care, and many report heightened anxiety, worry and frustration about their parenting role [23,24]. Most parents display signs of stress and anxiety within a very short time of their child’s diagnosis [25] and typically report grief, loss and relationship stress as well as family and work disruption [26]. Thus, in addition to care and support for the adolescent with T1D, attention to parenting and the needs of parents is warranted.

Parenting programs have been shown to be effective in producing positive outcomes for both parents and their children across a diverse range of childhood behavioral and health difficulties [27-29]. Programs that provide parents with strategies to help them build and maintain supportive relationships with their adolescent and to deal with the difficult behaviors that arise during the adolescent years have been shown to be particularly effective [30,31].

While a number of reviews have demonstrated some benefits of family interventions in improving outcomes for children with T1D [12,32], such interventions have primarily focused on improving treatment adherence behaviors [12,33] rather than easing the psychological burden of the disease. Interventions for adolescents that focus on increasing coping and teaching problem solving skills have been found to be effective in addressing the psychological barriers to self-management when delivered across a range of modalities, although their impact on longer term adherence and metabolic control is yet to be established [34].

Interventions that target *both* the adolescent and their parent offer the potential to prevent mental health problems in the adolescent through affecting the context in which adolescent difficulties occur, as well as improving parent well-being [35-38].

### The service context

The current availability of intervention and support for families with a child with T1D is variable, as is the way in which families cope with the illness [26]. Little attention has been given to provision of support for parents that assists them to deal with the emotional impact of their child’s health condition or their own well-being [39]. Such a focus appears important given the documented links between parent well-being and child outcomes found in the child development, risk and protection literature [40,41]. Furthermore, not all families have easy access to health services and those experiencing geographical or social isolation or who are unable to access health services due to time, transport or other constraints are at increased risk due to limited or no contact with professional and other supports.

While research shows that individual and group face-to-face interventions have been effective, the internet is one potential avenue for improving the accessibility of interventions that may otherwise be difficult to access due to geographic and social isolation. There is growing evidence for the efficacy of online mental and physical health interventions targeting young people (see [42-44]) and for parents of young people with T1D [45] demonstrating the viability of an internet intervention for adolescents with T1D and their parents. An internet-based intervention is also likely to be more engaging for adolescents who are early adopters of new technology [46], and for parents and adolescents for whom access to conventional services is not possible due to geographical and/or social isolation (e.g., due to study or work commitments). Most people, including those from disadvantaged backgrounds, have access to the internet, with approximately 95% of 15 to 25 year olds, 96% of 35 to 49 year olds, and 84% of 50 to 64 year olds regularly using the internet in Australia [47,48] – similar rates to those observed in the United States [49]. Taken together these findings support the use of internet-based health programs for education about, and prevention and treatment of psychological distress, and enhancement of optimal self-management of chronic illness during adolescence.

### The current study

This paper presents the study protocol for the randomized controlled trial (RCT) of the *Nothing Ventured Nothing Gained* intervention (*NVNG*), an online adolescent and parenting intervention that aims to improve the physical and mental health outcomes of adolescents with T1D and their parents. To date, there is no published research on the efficacy of online interventions with both an adolescent *and* parenting component that aims to improve outcomes for adolescents with T1D.

### Primary outcomes

Primary outcomes will be adolescent mental health (depression and anxiety). Our primary hypothesis is that adolescents randomized to receive the *NVNG* intervention immediately, will demonstrate significantly better mental health (lower levels of depression and anxiety) than adolescents in the wait-list control group, from pre- to post-intervention and at the 6 month follow-up.

### Secondary outcomes

Secondary outcomes will be adolescent behavioral (diabetes self-management and risk taking behavior), psychosocial (diabetes relevant quality of life, parent reported child well-being, self-efficacy, resilience, and perceived illness benefits and burdens); metabolic (HbA1c) outcomes; parent psychosocial outcomes (negative affect, fatigue, self-efficacy and parent experience of child illness); as well as adolescent and parent reported family outcomes (parent-adolescent communication, responsibility for diabetes care, diabetes related conflict). Our secondary hypotheses are: a) Adolescents randomized to receive *NVNG* immediately, compared to those who are required to wait for 6 months, will demonstrate significantly greater improvements in well-being (diabetes quality of life, parent-reported well-being), cognitive (self-efficacy, resilience, perceived illness benefits and burdens), and behavioral (diabetes self-management, reduced risk taking) outcomes from pre- to post-intervention and at the 6 month follow-up; b) Parents randomized to receive *NVNG* immediately, compared to those who wait for 6 months, will demonstrate significantly better mental health (lower levels of depression, anxiety and stress), from pre- to post-intervention and at the 6 month follow-up; and c) Parents and adolescents randomized to receive *NVNG* immediately, will demonstrate significantly greater improvements in family communication, family conflict, and shared responsibility for diabetes management than that observed in the wait-list control group.

The results of this study will provide valuable information about the efficacy, acceptability and therefore the viability of delivering online intervention to families affected by chronic illness such as T1D.

## Methods/Design

The study will evaluate the efficacy, acceptability, and usability of the *NVNG* intervention with approximately 120 adolescents with T1D and their parents in Victoria, Australia. An RCT design, using repeated measures with two arms (intervention and wait-list control), will be used to assess the efficacy of the *NVNG* intervention. Outcomes for participants in both study arms will be assessed at three time points, at baseline (Time = 0), post-intervention/wait (Time = 6 weeks) and follow-up (Time = 6 months).

### Ethics approval

Ethics approval has been obtained from the Human Research Ethics Committees from the Royal Children’s Hospital (No. 29134) and Southern Health (No. 12103B).

### Participants

In Victoria Australia, the majority of adolescents with T1D receive their diabetes care from diabetes clinics within the state hospital system, by attending diabetes clinics approximately 3-monthly. This study will recruit adolescents and their parents from the two major pediatric diabetes clinics in Melbourne and their associated rural outreach clinics in Hamilton and Horsham, Victoria.

A rolling recruitment strategy will be used to recruit approximately 120 adolescents (60 intervention, 60 wait-list control group) with T1D, and one of their parents/guardians (n =120; 60 intervention; 60 wait-list control group). Researchers from the team will attend all pediatric diabetes clinic sessions over the course of four months for the purpose of face to face recruitment. Given that adolescents attend clinics 3-monthly, this will ensure that they reach all potential participants.

### Eligibility criteria

For adolescents, eligibility criteria will be a diagnosis with T1D, age between 13 to 18 years, access to the internet, and signed parental consent. For parents, eligibility criteria will include having a child aged between 13 and 18 years who has T1D, and access and ability to use the internet. Because the intervention and study questionnaires are available only in English language, adolescents and parents who are unable to understand spoken and written English will be excluded from participation.

### Sample size calculation

Given that there are no meta-analyses available for internet interventions of family centered parenting and adolescent programs, studies reporting face-to-face parenting and adolescent interventions and internet interventions directed at health behavior change were used to inform power calculations [50]. A meta-analysis of psychological interventions to improve outcomes in children and adolescents with T1D reported a moderate effect of family therapy on child/adolescent psychological distress (ES = .46) and HbA1c (ES = .41) [51]. A meta-analysis of internet interventions aiming to promote adolescent health related behaviors showed moderate effects (ES = .33) for interventions grounded in Cognitive Behavioral Theory or Theory of Planned Behavior [44]. Therefore a medium effect size is expected on the primary adolescent mental health outcome measure, as measured by the CDI and the RCMAS-S, between the two groups across the three assessment points. To power the study at the 80% level, based on an alpha level of .05, with an estimated medium effect size (.40) and with two groups over three assessment points, 64 complete responses will be required. Given that self-help online intervention studies often report high attrition rates (e.g. [52,53]), we have allowed for a 30% attrition rate between baseline and pre-assessment, and a further 20% attrition rate between post and follow-up; therefore a total of approximately 120 participants will be required; 60 per group.

### Recruitment

Participants will be recruited during routine visits to their diabetes clinic, where researchers will introduce the study in person to all families who meet the eligibility criteria. Those who express an interest will be given a Participant Information and Consent Form and a Registration Form to complete and return to the researchers in a reply paid envelope. Parents will be asked to nominate the primary and secondary carer in their family. Only the primary carer will participate in the study. Whilst the researchers acknowledge that it would be preferable for both parents to participate where possible, the limitations in terms of sample size, mean that if some participants had two parents and some only one, intervention dosage would be a potential confound. Participants will also be recruited via online methods including advertising on websites and in newsletters of peak Diabetes organizations. Potential participants who contact the researchers to express an interest and who meet the eligibility criteria will be sent the Participant Information and Consent Form and Registration Form by mail.

### Study arms

Participants will be randomized to one of two treatment arms: Intervention or wait-list control. Participants from both the intervention and control arms of the study will continue to receive usual care form their regular diabetes clinics throughout the study. Participants in the Intervention arm will receive immediate access to the *NVNG* intervention. Following randomization, participants in the wait-list control arm will be told that they are on a waiting list for 6 months after which time they will be given access to the intervention. During the waiting period they will be sent email or text message reminders to complete their post and follow up questionnaires but will have no other contact with the research team during that time.

### Randomization procedure

In accordance with CONSORT guidelines [54,55], randomization will occur after participants have completed their baseline questionnaire. A Hypertext Pre-processor (PHP) randomization algorithm method will be used to randomize participants into one of the two study arms. Those who are randomized to the intervention arm will be given immediate access to the online intervention and those randomized to the control arm will be placed on the waiting list and given access to the intervention 6 months after completing the post questionnaire. The CONSORT diagram showing the flow of participants through the study is shown in Figure 1.

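### The protocol gives two dates for control access, about 6 weeks apart, and the earlier one opens access just as the 6-month follow-up falls due

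*Protocol article*

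**What the plan says.** All of this is in the protocol article.

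- **Study arms:** following randomization, controls are told that "they are on a waiting list for 6 months after which time they will be given access to the intervention". The same section adds: "During the waiting period they will be sent email or text message reminders to complete their post and follow up questionnaires".
- **Randomization procedure:** "randomization will occur after participants have completed their baseline questionnaire". Controls then go on the waiting list and are "given access to the intervention 6 months after completing the post questionnaire".
- **Abstract, Method/Design:** "Participants will be randomized to receive the intervention immediately or to wait 6 months before accessing the intervention". This ties a 6-month wait to randomization by implication.
- **Secondary outcomes:** the comparison group is described by the phrase "compared to those who are required to wait for 6 months". This gives a length of wait but no starting point.
- **Methods/Design:** both arms are assessed at baseline (time 0), then at "post-intervention/wait (Time = 6 weeks) and follow-up (Time = 6 months".
- **Primary outcomes:** the arms are to be compared on depression and anxiety "from pre- to post-intervention and at the 6 month follow-up".

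**The concern.** The contradiction lies mainly between Study arms and Randomization procedure. One starts the 6 months at randomization, the other at the post questionnaire. The Abstract supports the first by implication, and the Secondary outcomes section is compatible with either.

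The choice matters because a wait-list contrast is clean only while controls have not had the programme. The 6-month comparison is part of the primary hypothesis. If access opens on the day that questionnaire falls due, nothing separates the last control measurement from exposure. A control who replies late and has already worked through some of the programme answers as a partly treated participant. The intervention is self-directed and online, so a control can start as soon as access opens. The resulting bias would run towards no difference.

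**Working it through.** **Inputs**

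- Randomization directly follows the baseline questionnaire, so it is taken as time 0 (Randomization procedure). Any delay would move the Study arms access date later by the same amount.
- Post questionnaire: week 6. Follow-up: 6 months from time 0 (Methods/Design).
- 6 months = 6 × 365.25/12 = 182.6 days, or about 26 weeks.

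**Access dates and margins**

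| Rule | Control access | Follow-up due | Margin |
|---|---|---|---|
| Study arms: 6 months from randomization | day 183, about week 26 (6.0 months) | about week 26 | 26 − 26 = 0 weeks |
| Randomization procedure: 6 months from post questionnaire, completed on time | 42 + 182.6 = day 225, about week 32 (7.4 months) | about week 26 | 32 − 26 = 6 weeks |

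If the post questionnaire is late, the second rule moves access later still: to 7.8 months if it is 2 weeks late and 8.3 months if it is 4 weeks late.

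**Longest possible access before a late reply**

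For a control whose 6-month questionnaire arrives L weeks after it is due:

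- Study arms rule: L weeks of access.
- Randomization procedure rule, post questionnaire on time: max(0, L − 6) weeks.

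A reply 4 weeks late could therefore follow up to 4 weeks of access under the first rule and none under the second. These are limits on access; actual use may be less.

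**Can the two rules be reconciled?**

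The obvious attempt is to start the 6-month wait at the post questionnaire. Study arms rules this out. It has controls reminded about the post questionnaire during the wait, so the wait must begin before that questionnaire is completed. Randomization procedure also puts controls on the list at randomization, which makes its own total wait about 7.4 months, not 6.

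**Size of the bias**

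If a share p of the control 6-month replies comes after programme use, and those controls have gained on average a fraction f of the effect, the 6-month contrast shrinks by the proportion p × f. The document gives neither p nor f, so no figure follows from it.

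**The case against.** The strongest reply is that the intended order is clear and sound. Reminders for both later questionnaires fall within the wait, so follow-up is meant to come first and access second. Only the Randomization procedure section ties access to a questionnaire, and it leaves about 6 weeks. The Study arms sentence reports what participants are told and may be a rounded description. Harm needs three things together: the earlier clock in use, a late reply, and programme use before that reply. The document shows none of them happening. Reply windows are also the kind of detail that an article leaves to the full protocol, and Figure 1 is not available here.

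Much of this stands. It limits the consequence and rules out any claim that control data are contaminated in general. It does not remove the conflict. Two rules are stated, they give different dates, and no text shown says which governs. If the later rule is the true one, controls are being told a wait about 6 weeks too short.

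Three stronger readings are tempting, and the document does not support them:

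- **That four sections contradict one another.** Secondary outcomes gives only a duration, and the Abstract only implies the starting point.
- **That access opens before the follow-up.** This would hold if follow-up were counted from the post questionnaire, but Methods/Design lists the 6-month point on the same scale as baseline at time 0.
- **That the planned effect of .40 would shrink by a stated amount.** The Sample size calculation section sets .40 for the difference across all three assessments, and the 6-week contrast is unaffected. Any figure would also need invented values for p and f.

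**Conclusion.** The protocol gives two control access dates about 6 weeks apart, and both cannot be followed. Under the earlier one the margin between the 6-month follow-up falling due and control access is about 0 weeks; under the later one it is about 6 weeks. This rests on randomization close to baseline and, for the later date, on a post questionnaire completed on time.

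Controls who reply on time are unexposed under either rule. The risk is confined to late control replies after programme use under the earlier clock. It would bias the 6-month part of the primary hypothesis towards no difference, by an amount that the document does not allow anyone to calculate. The matter should be fixed, because the contrast at risk is a primary one and the protection is cheap. It is not evidence that the trial's results are compromised.

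**What to change.** 1. State one clock, counted from randomization, in Study arms and in Randomization procedure. The Abstract and Secondary outcomes then follow.
2. Open control access only when the 6-month questionnaire has been returned or a stated window has closed, whether or not the post questionnaire was returned. The last part matters because a rule triggered by the post questionnaire gives no access date to a control who never completes it, and the sample size calculation itself allows for substantial attrition.
3. Trial status says that data collection is under way. For controls already given access, keep all their data in the intention-to-treat analysis. Report how many control 6-month questionnaires are dated after access opened and, if log-in dates are recorded, how many are dated after a first log-in. Process measures mentions only the percentage of modules accessed, so log-in dates should not be assumed to exist.
4. If a sensitivity analysis uses a questionnaire-date cut-off, count it from randomization and apply it to both arms. Removing late controls alone would introduce a selection difference between the arms.

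The cost is a wording change in two sections, one access rule, and one count (two if log-in dates exist) from access-opening and questionnaire dates. The downside is that some controls wait a few weeks longer for the programme.
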